Read together, these studies establish that the capability frontier—biometric facial representation, autonomous plan generation, and the connected infrastructure that carries both—is advancing fastest on the consumer side, where devices and data leave the clinical setting, and the person concerned has the least oversight. What none of them establish, and what remains unresolved, is whether the people whose faces, physiology, and devices are involved regard these arrangements as acceptable, whom they hold responsible when such systems err, and at which point along the autonomy continuum their acceptance breaks down. Technical validation is reported as accuracy against benchmarks and as robustness under attack; acceptability is a distinct empirical quantity with its own measurement requirements, and it cannot be inferred from either. Two consequences follow for the present protocol. First, the autonomy levels examined here are not speculative: each corresponds to a capability already realized or under active development, so the attitudes measured are attitudes toward systems that patients may encounter. Second, the design isolates the quantity the technical literature leaves unmeasured—it holds the clinical task constant, varies only the degree of machine autonomy, and records acceptability, trust, perceived risk, and responsibility attribution within person, so that the location and shape of any decline in acceptance can be estimated rather than assumed.

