
### 2.2. Experimental Vignettes

The four vignettes describe distinct configurations of AI involvement in facial reconstructive surgical planning, varying both the AI’s task (imaging analysis, decision support, outcome simulation, autonomous planning) and the surgeon’s level of supervision (Table 1). Each configuration corresponds to a capability documented in the current literature: anatomical structure analysis from CT [6,8], algorithmic generation of candidate surgical plans [9], three-dimensional simulation of postoperative facial appearance [12,13], and highly autonomous planning of the kind anticipated by surgical-autonomy frameworks [14,15]. All vignettes open with an identical premise (the respondent needs facial reconstructive surgery following an injury) and are written in parallel second-person wording of comparable length and reading difficulty, so that scenario content—not framing—drives differences in responses. Because the four configurations differ in what the AI does as well as in how much the surgeon decides, a perceived difference between them could in principle reflect technical sophistication rather than autonomy. Three features are intended to keep the two apart. First, every vignette closes by stating explicitly how the final surgical plan is reached and by whom. In Scenarios A–C, a single clause of parallel construction names the surgeon as the decision-maker (making all decisions, choosing among the proposed options, or deciding the final plan after reviewing the simulations); in Scenario D, the closing sentences state that the surgeon reviews the AI’s plan but rarely modifies it. What varies is therefore the decisional locus, not the computational task. Each comprehension check is built on that same feature: the decision-maker in Scenarios A and B; the role of the system in Scenario C (whose decisional clause is functionally equivalent to Scenario B’s, so that the role is what distinguishes the two); and the origin of the plan actually followed in Scenario D. Second, the vignettes are matched on the quantity of technical detail supplied—one sentence describing the system’s input and output in each case—so that described sophistication does not rise in step with autonomy. Scenario C specifies a generative three-dimensional simulation, computationally the most elaborate output in the set, yet leaves the decision entirely with the surgeon; Scenario D describes a comparatively conventional optimization whose distinguishing feature is decisional rather than technical. Third, two manipulation checks follow every scenario: MAN1, perceived control of the AI over the final decision, and MAN2, perceived technical sophistication of the system. The manipulation is treated as valid only if MAN1 orders the scenarios as intended; MAN2 verifies that sophistication does not itself increase monotonically with autonomy and enters a pre-specified sensitivity analysis as a covariate, so that the autonomy effect can be estimated with perceived sophistication held constant (Section 2.9.1). The full vignette texts are provided in Appendix A.

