## 3. Expected Results

Based on the algorithm-aversion and trust studies [19,37,38], we expect acceptability and trust to decline—and perceived risk to rise—across the autonomy gradient from Scenario A to Scenario D, with the largest drop anticipated at the transition to autonomous planning (Scenario D), where the surgeon’s corrective role is described as residual. Whether that decline is a gradient or a step is an open question that the design is equipped to address: a step would show as a substantial quadratic or cubic component alongside the linear one, and its location would be identified by the adjacent-pair contrasts, which we expect to place the largest single drop at C–D. Nor do we assume the pattern is homogeneous across participants; a substantial random-slope variance would itself be informative, indicating that an average trajectory conceals distinct groups of respondents rather than describing a shared response. The expectation of decline is, in any case, consistent with survey evidence that public comfort is conditional on physician supervision [24,25,31]. For responsibility attribution, we expect the surgeon to be assigned the dominant share in low-autonomy scenarios [41], with a progressive migration toward the AI developer—and possibly a diffusion of responsibility across actors, indexed by falling Herfindahl concentration—as autonomy increases [44,45]. We expect the manipulation check (perceived AI control) to order the scenarios from A to D within each of the four presentation sequences, validating the experimental gradient independently of serial position, and we expect no scenario × sequence interaction. Should one nevertheless appear, the position-adjusted mixed-model estimate becomes the primary basis for interpreting H1–H3, and the magnitude of the order effect will itself be reported as a finding about the stability of vignette-based autonomy judgments. Given the design’s sensitivity (power of 0.99 against small within-subjects effects at ρ = 0.50, and 0.95 at ρ = 0.30, for the target sample), a null result for a primary hypothesis would place a tight upper bound on the size of any autonomy effect rather than leaving the question open; the pre-specified equivalence tests of Section 2.9.1 make that bound explicit rather than infer absence from non-significance [70]. The moderation hypothesis (H4) is powered only for medium-small interactions and will be interpreted with corresponding caution. Results will inform the ordering of public concerns along the assistance-to-autonomy continuum and identify which implementation configurations are publicly acceptable entry points for surgical AI in Romania.

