Several limitations are accepted by design and will be declared in the results article. First, the sample is a self-selected online convenience sample: results describe Romanian adults active in digital environments—likely younger and more educated than the general population—and do not support national generalization; the sample structure will be reported against National Institute of Statistics reference data. Second, the vignettes are hypothetical, and the distance between a vignette judgment and a decision taken in a consulting room is not merely one of degree. Participants evaluate a scenario in which they are not injured, not in pain, not facing a scheduled operation, and not choosing between real surgeons. They bear no consequences for the judgment they record, receive no counseling, and cannot ask questions. Above all, they are not exposed to the most influential element of real surgical decision-making: a conversation with the clinician who would operate, whose endorsement and explanation are known to shift acceptance of AI-supported care substantially [27,28]. Stated acceptability under these conditions is best read as a measure of prior disposition toward a described scenario rather than as a prediction of consent behavior. The ordering of the scenarios is likely to be more robust than the absolute levels, which could be lower than those a counseled patient would report or higher if hypothetical risk is discounted. This is a standard limitation of vignette methodology [61,62], and the remedies lie outside the present design: replication among patients actually scheduled for facial reconstructive surgery, and ultimately observation of consent decisions where such systems are in use. Third, presentation sequence is counterbalanced but not thereby rendered irrelevant. The Williams square balances serial position and first-order carry-over, so that the autonomy effect is estimable free of both, but no four-sequence design balances higher-order carry-over—a participant’s evaluation of the third scenario being shaped jointly by the first two—and contrast effects that depend on which scenario was seen immediately before therefore remain possible. The scenario × sequence interaction, the position-adjusted model, and the difficulty covariate bound the magnitude of what remains; they do not remove it, and a large residual would warrant a between-subjects replication in which each participant evaluates a single scenario. Fourth, demand and contrast effects are inherent to within-subjects designs: seeing all scenarios, participants may infer the study objective and exaggerate differentiation between scenarios; comparisons remain internally valid, but absolute difference magnitudes warrant caution. Fifth, all measures share a common method and a single measurement occasion, in a rapidly evolving attitude domain [38]. Sixth, the survey platform does not record completion time, so quality control relies on embedded checks rather than temporal filters [69]. Seventh, the demographic and familiarity subgroups formed within a convenience sample of 300 will differ substantially in size, and several will be small; the minimum-cell rule of Section 2.9.2, and the requirement that subgroup differences be inferred only from formal interaction terms, are intended to forestall the familiar error of asserting a difference from a significant effect in the larger subgroup together with a non-significant one in the smaller. None of these limitations is unusual for online vignette experiments, and declaring them in advance is intended to keep the eventual findings interpretable at their proper scope.

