## Figures and Tables

**Figure 1 healthcare-14-03030-f001:**
[figure not shown]
Achieved power of the primary repeated-measures ANOVA (four within-subject levels, α = 0.05) as a function of the number of valid responses, for small (*f* = 0.10, at ρ = 0.50 and ρ = 0.30) and medium (*f* = 0.25) effects. Dotted reference lines mark power = 0.80 and the two pre-specified thresholds (*N* = 140, minimum analyzable; *N* = 300, recruitment target). Curves are computed analytically from the noncentral *F* distribution. Entering presentation sequence as a between-subjects factor consumes three degrees of freedom from the error term and leaves these curves unchanged to within rounding.

**Table 1 healthcare-14-03030-t001:** The four experimental scenarios. The labels A–D denote autonomy level, not position in the sequence; scenarios are administered in one of four counterbalanced sequences (see Section 2.1).

Scenario	Label	Role of the AI System	Role of the Surgeon
A	Imaging assistance	Analyzes the CT scan and highlights anatomical structures (e.g., bone density, tissue layers)	Independently interprets the AI output and makes all decisions on the surgical plan
B	Decision support	Proposes three possible surgical plans, each with different advantages and disadvantages	Reviews all options, selects the most suitable plan, and may adjust it
C	Outcome simulation	Generates 3D simulations of postoperative facial appearance for each surgical option	Reviews the simulations, discusses them with the patient, and decides the final plan
D	Autonomous planning	Generates a complete, optimized surgical plan	Reviews the plan before surgery; modifications to the AI proposal are rare

**Table 2 healthcare-14-03030-t002:** Minimum detectable effects (power = 0.80, α = 0.05).

Test	Parameters	Minimum Detectable Effect
RM-ANOVA, 4 within-subject levels	*N* = 24, ρ = 0.50	*f* = 0.25 (medium)
RM-ANOVA, 4 within-subject levels	*N* = 140, ρ = 0.50	*f* = 0.10 (small)
RM-ANOVA, 4 within-subject levels	*N* = 300, ρ = 0.50	*f* = 0.07
Dependent pairwise comparison	*N* = 300, α = 0.05	*dz* = 0.16
Dependent pairwise comparison	*N* = 300, α = 0.05/6	*dz* = 0.20
Scenario × familiarity interaction (*df* = 3)	*N* = 300, α = 0.05	*f*^2^ = 0.037
Goodness-of-fit chi-square, preference (*df* = 5)	*N* = 300, α = 0.05	*w* = 0.21
Autonomy main effect, sequence as between-subjects factor (*df* = 3)	*N* = 300, ρ = 0.50	*f* = 0.07

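### In Table 1 only Scenario C includes a discussion with the patient, so the B–C and C–D contrasts mix autonomy with patient involvement

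*Protocol article*

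**What the plan says.** Table 1 describes the surgeon's role in each scenario. In A the surgeon interprets the AI output alone and decides. In B the surgeon "Reviews all options, selects the most suitable plan, and may adjust it". In C the surgeon "Reviews the simulations, discusses them with the patient, and decides the final plan". In D the surgeon "Reviews the plan before surgery; modifications to the AI proposal are rare". The patient appears in C only.

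Section 1.4 says of the design that "it holds the clinical task constant, varies only the degree of machine autonomy". Section 2.2 opens by saying that both the AI's task and the surgeon's supervision vary. It says the vignettes "are written in parallel second-person wording of comparable length and reading difficulty" and concludes: "What varies is therefore the decisional locus, not the computational task". It treats the decision clauses of B and C as functionally equivalent. Technical sophistication is the only rival explanation it discusses, and MAN2 is the measure it provides for that.

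In Section 2.9.1 the location of any break is read only from the Holm-corrected adjacent pairs A–B, B–C and C–D. Section 3 refers to these contrasts, "which we expect to place the largest single drop at C–D", and gives as the reason the surgeon's residual corrective role in D. Section 4 lists among the things vignette participants do not experience "a conversation with the clinician who would operate, whose endorsement and explanation are known to shift acceptance of AI-supported care substantially".

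**The concern.** On the protocol's own account, talking with the operating clinician is linked to acceptance of AI-supported care. A description of such a talk in one scenario only is a second difference between C and its neighbours, beyond who decides. It stays with C in all four Williams sequences, so counterbalancing and the serial-position term cannot separate it. MAN1 measures perceived AI control, MAN2 sophistication and DIF1 difficulty; none measures patient involvement. The rewording triggers in Sections 2.6 and 2.8 do not cover it, and the limitations in Section 4 do not declare it.

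At stake is one of the study's headline questions: where along the continuum acceptance erodes, and whether it does so gradually or in a step. C enters two of the three contrasts that answer it. A shift in C acts on those two in opposite directions.

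**Working it through.** **Inputs from the protocol.** N = 300; six pairwise comparisons with Bonferroni bound 0.05/6; smallest effect of interest dz = 0.20, with equivalence tests against that bound (Sections 2.5 and 2.9.1, Table 2).

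**Input assumed.** A favourable shift *s* in Scenario C alone, in units of the SD of a paired difference, taken equal for all pairs. The documents give no value, so I use *s* = 0 to 0.30. For perceived risk the signs are mirrored.

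**Step 1: the plan's own figures.** Paired two-sided t test, df = 299, noncentrality dz × √300 = dz × 17.32. The smallest dz detectable with power 0.80 is 0.162 at α = 0.05 and 0.202 at α = 0.05/6. Table 2 states 0.16 and 0.20, so both reproduce.

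**Step 2: what a shift in C does to the adjacent drops.**
- A–B is unchanged.
- B–C observed = B–C due to autonomy − *s*.
- C–D observed = C–D due to autonomy + *s*.

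**Step 3: a true straight decline of 0.20 per step.** The means are 0, −0.20, −0.40, −0.60.

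| *s* | A–B | B–C | C–D |
|---|---|---|---|
| 0 | 0.20 | 0.20 | 0.20 |
| 0.10 | 0.20 | 0.10 | 0.30 |
| 0.20 | 0.20 | 0.00 | 0.40 |
| 0.30 | 0.20 | −0.10 | 0.50 |

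At *s* = 0.20 the means are 0, −0.20, −0.20, −0.60. The sums of squares are:
- linear: 1.8² / 20 = 0.162
- quadratic: 0.2² / 4 = 0.010
- cubic: 0.6² / 20 = 0.018

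The total is 0.190, so the linear share is 85% and the non-linear share 15%. A large linear component with some curvature, and the largest adjacent drop at C–D, is the pattern Section 2.9.1 would take as a step. With B and C equal in the data, the planned equivalence test would declare them equivalent with probability about 2Φ(3.46 − 1.65) − 1 = 0.93. The false step would then have formal support.

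**Step 4: no autonomy effect at all.** C–D is significant at 0.05/6 with probability 0.18, 0.79 and 0.99 for *s* = 0.10, 0.20 and 0.30. B–C shows a rise of the same size. The shape is 7% linear, 33% quadratic and 60% cubic.

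**Step 5: effect on the trend test of H1.** With weights −3, −1, 1, 3, the linear contrast in the Step 3 example has absolute size 2.0 without the shift and 1.8 with *s* = 0.20, a 10% attenuation. A–B, A–D and B–D do not contain C and do not change.

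**The case against.** Table 1 is a summary. Participants read the vignettes in Appendix A, whose full text is not at hand, and Section 2.2's paraphrase of C's closing clause does not mention the discussion. This stands as a condition on the finding: the first step is to check the texts.

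Section 4 speaks of a real conversation, with endorsement and explanation, to which participants are not exposed. A half-sentence in a vignette may do much less, or nothing. This also stands, and is why the assumed range starts at zero and the direction is an assumption.

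A reader might infer that the predicted C–D drop is built into the vignettes. The documents do not support that. Section 3 bases the prediction on the surgeon's residual role in D, which is the intended manipulation; the clause could add to a C–D drop but is not the stated reason for one. Nor is it shown that the H1 and H2 trend tests are inflated: a favourable shift in C slightly weakens the linear trend.

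Finally, a shift in C with no true decline would produce a visible rise from B to C, which Section 2.9.1 commits to reporting as non-monotone. That is right. The misleading case needs a true decline as well, but a decline is what H1 predicts.

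**Conclusion.** The concern holds in a limited form. As Table 1 describes the scenarios, B–C and C–D each mix autonomy with patient involvement, contrary to the statements in Sections 1.4 and 2.2 about what varies, and nothing in the plan separates the two. If the clause raises acceptability, B–C shrinks or reverses and C–D grows by the same amount. A shift equal to the plan's own smallest effect of interest (dz 0.20) is enough to make a straight decline of 0.20 per step look like a break at C–D.

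The damage is confined to locating the break through those two contrasts. The size and direction of the clause's effect are assumptions, and whether the administered texts match Table 1 remains to be confirmed.

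**What to change.** 1. Check the full vignette texts in Appendix A for any mention of contact with the patient.
2. Before the pilot, and within the ethics amendment that Sections 2.10 and 2.12 describe as still to be submitted, delete the patient-discussion clause from Scenario C. This is preferred to adding it elsewhere, because a discussion in D could enlarge the surgeon's residual role there and weaken the manipulation. The alternative is one identical neutral sentence in all four vignettes.
3. Change the statement in Section 1.4 so that it agrees with the opening of Section 2.2, which says that both the AI's task and the supervision vary.
4. If the clause is kept, declare the confound among the limitations, state what B–C and C–D can then show, and use B–D, which does not involve C and is already among the six planned pairs, to support any claim about the move to autonomous planning.

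No data have been collected, so the cost is one edit to the wording and slightly less natural prose in Scenario C. After data collection the clause cannot be separated from Scenario C.
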